#### Blood pressure and heart rate variability

Blood pressure and heart rate variability will be obtained in the supine position after 10 min of rest by an evaluator blinded to other assessments and group allocation. Brachial auscultatory blood pressure will be measured in triplicate on both arms using a sphygmomanometer and a stethoscope (BIC, Standard, Brazil) considering phases I and V of the Korotkoff sounds for the identification of systolic and diastolic blood pressures, respectively. The mean of three measured values, with at least 4 mmHg of difference between them on each arm, will be calculated. The mean value obtained on the arm with the higher blood pressure will be considered for the analysis [74].

For the determination of resting heart rate variability, RR intervals will be obtained by a heart rate monitor (POLAR – V800, USA) for 10 min. The evaluator will visually inspect all RR intervals and correct, via interpolation, any inappropriate or premature RR interval. Any RR interval with a difference greater than 20% of adjacent intervals will be filtered using a moving average algorithm. Normalized RR intervals will be transferred to a dedicated heart rate variability software package (Kubios HRV v 2.1, University of Eastern Finland, Finland) for further analysis. Using the recommendations of the Task Force for heart rate variability, the time-domain (SDNN, RMSSD, and pNN50) and frequency-domain parameters (low frequency, high frequency, and ratio between low and high frequency) will be analyzed and a non-linear analysis (SD1 and SD2) will be performed as previously described [75].

#### Blood sample collection

All fasting blood samples will be collected in additive-free tubes (serum), in K3-EDTA containing tubes (plasma), and in clot activation gel tubes (whole blood). Whole blood will be frozen immediately after collection of blood samples and stored at − 20 °C. The serum and plasma samples will be centrifuged at 3000 rpm for 15 min at 4 °C. Supernatants will be frozen and stored at − 20 °C until analysis. These samples will be analyzed for lipid profile (total cholesterol, HDL, LDL, triglycerides) and blood glucose levels (Ultrospec 6300 Pro), according to World Health Organization Guidelines [40] and the manufacturer’s instructions.

#### Clinical outcomes – scales of suicidal ideation, sleep, and BRIAN

The Columbia Suicide Severity rating scale distinguishes suicidal ideation from suicidal behavior. There are four subscales, namely severity of ideation (score of 0–5), intensity of suicidal ideation (score of 0–5), behavior (which is a nominal scale that evaluates actual, aborted, interrupted attempts, and self-injurious behavior, with no intent to commit suicide), and the fourth is the lethality of the actual attempts (scale score 0–6) [41].

The Scale of Hopelessness identifies the level of pessimism, which is directly related to the chance of developing several mental disorders and to suicide risk. The scale consists of 20 true–false questions. The total score is 20 points and each item is scored as 0 or 1 [42].

The Pittsburgh Sleep Quality Index score is a tool widely used for research and practice regarding psychiatric disorders [37]. This questionnaire interprets the perception of sleep quality in a feasible and reliable manner [37, 76]. The overall index is composed of seven components, namely subjective sleep quality (perception of sleep quality of subjects), sleep latency (time between lying on bed and sleeping), duration of sleep (sleeping period reported by the individual), sleep disturbance (sleeping problems), sleep medication (use of sleeping medications), and diurnal dysfunction (daytime sleepiness intensity). All the seven components are scored from 0 (no difficulty for the component of interest) to 3 (very bad). The scores on these components are combined to generate a global score that reflects the sleep quality and disturbances over a 1-month period. The overall score ranges from 0 to 21; if a patient reaches at least 5 points, they are diagnosed with an alteration of sleep. The higher the score the worse the quality of sleep.

The BRIAN is a self-report questionnaire designed to provide an index of disturbances in the circadian rhythm [38]. This scale considers sleep interruptions, irregularities in social rhythm, eating patterns, and abnormalities in daily activity at home and at work in the last 15 days, all of which are postulated to contribute to the onset and worsening of affective episodes, as well as psychosocial function and clinical outcomes [77–80]. The questionnaire includes 18 items divided into four domains of the circadian biological rhythm, namely sleep (5 questions), activity (5 questions), social (4 questions), and food patterns (4 questions). Each question is scored in 4-point subscales, with scores ranging from 1 (no difficulties in maintaining the usual pace) to 4 (serious difficulties in maintaining the usual pace), totaling a minimum and maximum overall score of 18 and 72, respectively. Higher scores indicate a greater rupture of the circadian rhythm. The chronotype is also captured by BRIAN, as the last three items address the individuals’ daily preference for work and sociability, if they feel more productive in the morning, and if they feel that their day and night cycle has been reversed over the last year. Three questions about circadian preference evaluate the morning and evening chronotypes: “Do you have more energy for work and interpersonal relationships at night?” (Active at night), “Do you feel more productive in the morning?” (Active in the morning), and “Have you reversed your day/night cycle?” (Reverse day/night cycle). The options are never (score of 1), rarely (score of 2), often (score of 3), or always (score of 4). A low score indicates a morning preference and a high score indicates a night preference [81].

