**Fig. 1 Fig1:**
[figure not shown]
Template of recommended content for the schedule of enrolment, interventions, and assessments

The primary outcome will be the change in the Montgomery-Åsberg Depression Scale (MADRS) score [28]. Secondary outcomes will be (1) cognitive function, assessed by Frontal Assessment Battery score [29], Trail Making Test A and B score [30], Rey’s Auditory-Verbal Learning Test (RAVLT) score [31], Digit Symbol Substitution Test score [32], Montreal Cognitive Assessment (MoCA) score [33], and Stroop test score [34]); (2) hippocampal volume assessed by magnetic resonance imaging (MRI) [35]; (3) BDNF expression [36]; (4) sleep parameters assessed by Pittsburgh Sleep Quality Index score [37], sleep quality assessment by accelerometry and the Biological Rhythms Interview of Assessment in Neuropsychiatry (BRIAN) score [38]; (5) cardiovascular risk assessed by global cardiovascular score, metabolic syndrome, waist circumference, blood pressure, lipid profile (total cholesterol, HDL cholesterol, LDL cholesterol, triglycerides), and glycemia [39, 40]; (6) suicidal ideation and behavior assessed by the Scale Columbia of Suicide score [41] and Scale of Hopelessness score [42]); (7) functionality assessed by gait linear spatial variables [43, 44], Timed Up and Go test (TUG) score [45], TUG cognitive score [46], handgrip strength [47], 6-min walk test [48] physical activity levels (sedentary time, active time, time spent in different physical activity intensities, energy expenditure, and number of steps per day), body weight, and hip and waist circumference [49]; and (8) treatment costs including laboratory procedures, medicines, and doctor consultations per patient [50].

The study will be conducted in accordance with theDeclaration of Helsinki revised in 2008 [51] and approved by the ethics committees of the Department of Health of the city of São Paulo and of the Hospital Israelita Albert Einstein, Certificate of Ethical Appreciation Presentation (PCEA) number 64888017.3.0000.0086. Trial registration is RBR-9zgxzd.

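### The stated direction of the BRIAN chronotype score is wrong for the morning-productivity item, which is coded upward with no reversal

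*Protocol article*

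**What the plan says.** All the relevant text is in the protocol article, under Clinical outcomes – scales of suicidal ideation, sleep, and BRIAN.

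- The main questionnaire has 18 items in four domains: "sleep (5 questions), activity (5 questions), social (4 questions), and food patterns (4 questions". Each item is scored 1 to 4, "totaling a minimum and maximum overall score of 18 and 72, respectively".
- Three questions address chronotype: "Do you have more energy for work and interpersonal relationships at night", "Do you feel more productive in the morning" and "Have you reversed your day/night cycle".
- One response coding is given for these questions: "The options are never (score of 1), rarely (score of 2), often (score of 3), or always (score of 4".
- The interpretation follows: "A low score indicates a morning preference and a high score indicates a night preference". It carries a reference to a scoring source that is not shown here.

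The article does not mention reverse-scoring of any item. It does not say how the three answers are combined, and it gives no range for a chronotype score. The outcome list under Study design includes "the Biological Rhythms Interview of Assessment in Neuropsychiatry (BRIAN) score" among the sleep parameters and does not name chronotype.

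**The concern.** The night question and the morning question point in opposite directions but share one upward coding. A single rule that low means morning and high means night cannot be true of both. The article gives the item wording, the coding and the interpretation, and the three do not fit together, so this is more than a detail left out for brevity.

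An analyst who followed the text literally would count morning productivity as evidence of night preference. Nothing in the output would reveal it, because every value would fall in a plausible range. At stake is whether any chronotype description or comparison reported from these items can be interpreted.

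**Working it through.** **Reproducing the article's own figure.** The items number 5 + 5 + 4 + 4 = 18. The minimum is 18 × 1 = 18 and the maximum 18 × 4 = 72, as stated. The four domains use up all 18 items and chronotype is not one of them, so the three chronotype questions lie outside this total.

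**Item by item (no assumption about combining).**

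| Item | Meaning of 1 | Meaning of 4 | Fits low = morning, high = night? |
|---|---|---|---|
| Active at night | never more energy at night | always | yes |
| Active in the morning | never productive in the morning | always | no, reversed |
| Reversed day/night cycle | never | always | yes, taking a reversed cycle as a night trait |

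**As a sum (assumption: the three answers are added).** Write N for the night item, M for the morning item and R for the reversed-cycle item, each from 1 to 4.

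- Stated score: S = N + M + R
- Keyed score: K = N + (5 − M) + R = S + 5 − 2M

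| Pattern (N, M, R) | S | K |
|---|---|---|
| Clear morning type (1,4,1) | 6 | 3 |
| Clear night type, cycle not reversed (4,1,1) | 6 | 9 |
| Clear night type, cycle reversed (4,1,4) | 9 | 12 |
| Often active at night, never in the morning (3,1,1) | 5 | 8 |
| Never to all three (1,1,1) | 3 | 6 |
| Always to all three (4,4,4) | 12 | 9 |

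Under S, the first two rows cannot be told apart. The (3,1,1) patient, at 5, appears more morning-oriented than the clear morning type at 6. The minimum of 3 requires never being productive in the morning, and the maximum of 12 requires always being so. Between (1,4,1) and (4,1,4) the gap is 9 − 6 = 3 points instead of 12 − 3 = 9.

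**Illustration over all 4 × 4 × 4 = 64 patterns, equally weighted.** The items are then independent with a common variance v.

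- Cov(S, K) = v − v + v = v, and Var(S) = Var(K) = 3v, so the correlation is v / 3v = 0.33.
- Cov(S, N − M) = v − v = 0, so the stated sum has zero correlation with the night-minus-morning contrast.
- K separates 1758 pairs of patterns. S orders 990 the same way, reverses 566 (566/1758 = 32%) and ties 202 (202/1758 = 11%). Check: 990 + 566 + 202 = 1758.

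**The case against.** The strongest reply is that the article never says the three answers are added. It speaks only of a low and a high score, and it gives no range, unlike the 18 to 72 for the main scale. The scoring is also attributed to a cited source that may reverse the morning item or report the items singly; the article may simply have abbreviated it. This stands as a limit: every figure based on a sum is conditional, and the text does not show that the trial's analysis will be wrong. It does not rescue the sentence, which is wrong for the morning item even when items are read one at a time. If the source does reverse the item, the article misdescribes it.

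A reader might infer that the BRIAN secondary outcome itself, or one of its domains, is corrupted and that treatment differences on it would shrink. The document does not support this. The domain counts leave no room for the three items in the total, and chronotype is absent from the outcome list, from the hypothesis in Background and from the outcomes named under Data analysis and power calculations. The text therefore already keeps these items out of the total.

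A reader might also take the 0.33 or the 32% as a forecast for these patients. The article gives no response distribution, so equal weighting only shows how the rule behaves.

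**Conclusion.** The point holds in a limited form. As written, the interpretation contradicts the coding of the morning item, and this can be seen from the article alone. If the items are summed without reversal, the result cannot separate a clear morning type from a clear night type whose cycle is not reversed (both score 6). The 0.33 correlation with the keyed sum rests on two further assumptions: equal weight on all 64 patterns, and a reversed cycle counting towards night preference.

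The consequence is confined to an ancillary descriptor. The BRIAN total, its four domains, MADRS and the sample size do not depend on it. This is a minor correction worth making.

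**What to change.** First check how the cited scoring source and the case report form key and combine the three items. If the form's coding is not already reversed, either score the morning item as 5 minus the response before combining, or report the three items separately and state the direction of each. In either case, amend the interpretation sentence so that it is true of the coding used. With the reversal and a sum, (1,4,1) scores 3 and (4,1,4) scores 12, and the stated reading becomes correct.

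The cost is one sentence and at most one line of code. The check must come first: applying the reversal to a form that already reverses the item would undo the correct keying.

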##### Clinical outcomes – functional tests

Linear spatial variables of gait will be assessed using three inertial sensors (GaitUp, Physilogs^®^, Switzerland), while participants walk on a 15 m walkway. Each of the three sensors encompasses a micro-controller, memory, three-axis accelerometer (range ± 3 g), a gyroscope (range ± 800° s − 1), and a battery comprising a small (50 mm × 37 mm × 9.2 mm) and lightweight module (19 g). Two modules are fixed in the foot and one is fixed in the lower back. These sensors will measure step length, gait speed, cadence, and percentage of oscillation, variables that have been previously validated to assess gait pattern in older adults [43, 44]. The participants will perform three trials on three different conditions, namely (1) single task (only walking); (2) dual task words (walking and speaking words); and (3) dual task subtractions (walking and serial –3 subtractions).

The TUG test [45] is one of the most used tests to assess the functionality of older individuals. The patient will be timed while rising from a chair (seat height 46 cm), walking as quickly as possible at a comfortable and safe pace to a line on the floor 3 m away from the chair, turning and walking back to the chair, and siting down again. Time will be recorded from the instant the patient’s buttocks leave the chair (standing up) until the next contact with the chair (sitting down). Before the test, the patients will perform two familiarization attempts separated by 1 min. After the familiarization trials, two test trials will be performed with a 1 min interval between trials [37]. The lowest time will be used for analysis.

The TUG cognitive test [46] will be identical to the TUG, but individuals will perform cognitive tasks (subtractions) during the test. The patients will say the results of serial –3 subtractions starting with different numbers [46] to eliminate any training effect. The lowest time will be used for analysis.

The handgrip strength will be assessed using a Jamar dynamometer (Lafayette Instrument Co, Lafayette, USA). The instrument has two parallel handles, one fixed and one movable. This instrument has a closed hydraulic system that measures the amount of grip strength when producing an isometric contraction of the hand muscles. Results will be recorded in kilograms. Patient’s position will follow the guidelines of the American Society of Hand Therapists [47], which positions the shoulder slightly adducted, the elbow flexed at 90°, and the forearm in a neutral position. The testing protocol consisted of three 5 s maximal isometric contractions performed with the dominant hand, with a rest period of at least 60 s. Two attempts will be performed on 2 separate days (test and retest, minimum interval of 48 h). The highest force value between the 2 days will be considered for analysis.

The 6-min walk test is an inexpensive, relatively fast, safe, and well tolerated method for assessing exercise capacity [48]. It consists of walking as far as possible in 6 min in a 30-m track [48]. Previous studies demonstrated the agreement (*r* = 0.59) (standard error of estimate = 3.82 mL/kg/min) of this indirect protocol with the gold standard protocol for VO_2max_ [82].

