### Setting

Patients with depression will be recruited in the southern region of the São Paulo city at the Basic Health Unit (BHU; i.e., Arariba Park) in the state of São Paulo, Brazil. This BHU is part of the Brazilian Unified National Health System. First, patients will be referred by the physician team of the BHU if they fulfil the criteria of being 40 years and older, being treated for depression, and have no absolute contraindication to perform physical exercise. After the initial screening, patients will be fully informed of the procedures involved in the present trial and invited to sign an informed consent form. Participants will visit the laboratory on six occasions to perform the following assessments (Fig. 2):Visit 1: Consent form and anamnesis, Mini International Neuropsychiatric Interview (MINI) [52], and MADRS scale [28]. The number of depressive episodes in life and medicine dosage in the last 3 months (necessary clinical adjustments) [53] will be assessed by a trained psychiatrist researcher. Patients diagnosed with depression (single episode or recurrent episodes) will be referred to Visit 2. Patients will be informed that they may terminate their participation in this trial at any time, regardless of the reason.Visit 2: Questionnaire of cognitive function, suicidal ideation and behavior, hopelessness, and sleep quality.Visit 3: Blood samples after a 12 h fasting, functional tests, and instructions to use the accelerometer (GT9X ActiGraph accelerometer, Pensacola, USA) to assess sleep quality.Visit 4: these visits will be used to estimate the typical error of the functional tests (TUG test, TUG cognitive test, handgrip strength, 6-min walk test, body weight, hip and waist circumference); an interval of 48 h will be granted between Visits 3 and 4.Visit 5: Ergometric test and presence of absolute contraindications to exercise.Visit 6: MRI of the brain and instructions to use the accelerometer (GT9X ActiGraph accelerometer, Pensacola, USA) to assess physical activity level.

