**Fig. 2 Fig2:**
[figure not shown]
Study design. First 4 weeks, the recruitment and initial test. For 24 weeks, the intervention period – training. Final 2 weeks, the Final tests. Visit 1 (V1): Consent form, Mini International Neuropsychiatric Interview (MINI), MADRS, number of depressive episodes in life, medicine dosage in the last 3 months (necessary clinical adjustments), and anamnesis. Visit 2 (V2): Questionnaire of cognition function, suicidal ideation behavior and sleep; Visit 3 (V3): Blood sample, functional tests, and accelerometer (sleep); Visit 4 (V4): functional tests. Visit 5 (V5): cardiorespiratory parameters; Visit 6 (V6): MRI of the brain and sleep quality (physical activity). After 24 weeks of intervention, all of the experimental groups will be reassessed at visit 7 to visit 11 (V7 to V11). V7: MRI of the brain and accelerometer (sleep); V8: blood sample; V9: MADRS, number of depressive episodes and medicine dosage; V10: Questionnaire of Cognition function, suicidal ideation behavior, sleep; V11: Functional tests and accelerometer (physical activity). At the end of the study, patient treatment costs will be estimated consulting the medical records of each patient. *HC* hip circumference, *WC* waist circumference

After 24 weeks of intervention, experimental groups will be reassessed in five visits (Visits 7–11; Fig. 2):Visit 7: MRI and accelerometer to assess sleep quality.Visit 8: Blood samples after 12 h of fasting.Visit 9: MADRS and necessary adjustments on medicine dosage [53] will be verified.Visit 10: Questionnaire of cognitive function, suicidal ideation and behavior, hopelessness, and sleep quality.Visit 11: Functional tests and accelerometer to assess the physical activity level.

At the end of the study, the patient treatment costs will be estimated [50, 54] by consulting the medical records of each patient.

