### Data analysis and power calculations

The Shapiro–Wilk and Levene’s tests will be used to determine normality and variance equality, respectively. Non-normal data will be log transformed. If the transformation does not produce a normal distribution, the effect of influential points in data analyses will be tested. If influential points change the interpretation of the results, they will be manually removed. Linear mixed models having group and time as fixed factors and patients as a random factor will be performed for each outcome (MADRS, clinical outcomes, hippocampal volume, brain-derived neurotrophic factor, cardiopulmonary parameters, lipid profile, and treatment costs) and domain (especially in clinical outcomes) [85]. In case an outcome presents pre-experimental period differences between groups, determined by a regular one-way ANOVA, an ANCOVA will be implemented having pre-experimental period values as covariates, group as a fixed factor, and patients as a random factor. An intention-to-treat analysis will also be performed in case of a high incidence of missing values, using linear mixed models; the first analysis will be performed removing the missing values, while the second analysis will be performed incorporating the missing data points to determine the impact of missing values in the overall results. Whenever a significant F-value is obtained, a post hoc test with a Tukey’s adjustment will be performed. In addition, within-group (pre- to post-changes) and between-group effect sizes will be calculated using Cohen’s d [86] for each outcome. Effect sizes will be classified as small (≤ 0.49), medium (0.50–0.79), and large (≥ 0.80). Finally, the level of significance adopted in the present study for all analyses will be *P* ≤ 0.05. Data will be presented as mean ± SD. SAS 9.2^®^ software (Institute Inc., Cary, NC, USA) will be used for the statistical analyses described. Considering the importance of the control of the error rates, typical error and coefficient of variation of the assessments will be performed under test and retest conditions in a sub-sample (10 subjects).

For the primary outcome (MADRS) the verification of status of depression (depressed, partial remission, full remission) and the number of patients in remission (< 10 points MADRS) will be verified [14, 87].

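### Handgrip is scored as the best of two days, but the schedule shows two test days before training and one after, so within-group change may be biased downward

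*Protocol article*

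**What the plan says.** Four parts of the protocol article bear on this.

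- **Clinical outcomes – functional tests (handgrip).** Each test is described thus: "The testing protocol consisted of three 5 s maximal isometric contractions performed with the dominant hand". It is repeated: "Two attempts will be performed on 2 separate days (test and retest, minimum interval of 48 h". The analysed value is then defined: "The highest force value between the 2 days will be considered for analysis". The rule is not limited to baseline.
- **Setting (baseline visits).** Functional tests take place at Visit 3 and again at Visit 4, with handgrip named among the Visit 4 tests: "an interval of 48 h will be granted between Visits 3 and 4". The stated purpose is typical error: "Visit 4: these visits will be used to estimate the typical error of the functional tests". No restriction to some of the patients is given here.
- **Follow-up visits and the Fig. 2 caption.** Of the five visits after training (7 to 11), only one includes functional tests: "Visit 11: Functional tests and accelerometer to assess the physical activity level". The caption agrees, with V3 and V4 before training and V11 after.
- **Data analysis and power calculations.** The linear mixed model for each outcome has group and time as fixed factors, and "within-group (pre- to post-changes) and between-group effect sizes will be calculated" for each outcome with Cohen's d. The same section places test-retest work in a sub-sample of 10 subjects.

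**The concern.** The maximum of several attempts rises with the number of attempts even when strength is unchanged. If baseline is the best of two days and follow-up the best of one, baseline is raised relative to follow-up by the scoring rule alone. The artefact runs downward in every arm: a true gain in the exercise arms is understated, and an unchanged control arm tends to show a loss.

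At stake are the time effect for handgrip and the within-group effect sizes that the article commits to report. The scoring rule and the visit list are both stated, and they do not fit together, so this is not a detail left to a fuller document.

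**Working it through.** The article gives no handgrip SD, typical error, reliability or expected change, so it has no handgrip figure to reproduce. The artefact can be derived in units of within-person SD.

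**Inputs from the article:** three contractions per test; two baseline test days (Visits 3 and 4); one follow-up test day (Visit 11); maximum taken over days; 75 patients, 25 per arm; a test-retest sub-sample of 10.

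**Assumptions:** normal within-person variation, three contractions on each day, no true change, and reliability (ICC) of 0.90 or 0.95. Cohen's d is taken to be standardised by the between-patient SD of a single-day score.

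**1. Contractions vary independently.** Baseline is the best of 6 and follow-up the best of 3. For standard normal values:

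E[max of 6] − E[max of 3] = 1.267 − 0.846 = 0.42 within-person SD.

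**2. All within-person variation is between days.** Baseline is the better of two day scores and follow-up is one day score:

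E[max of 2] − E[single] = 1/√π = 0.564 within-person SD.

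Simulated mixtures of day and contraction variation fall between these (0.50 with half the variance between days, 0.54 with 80%).

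**3. Conversion to d.** Multiply by √(1 − ICC).

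| Assumed ICC | √(1 − ICC) | Shift from 0.42 | Shift from 0.564 |
|---|---|---|---|
| 0.90 | 0.316 | −0.13 | −0.18 |
| 0.95 | 0.224 | −0.09 | −0.13 |

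If the reliability refers to the day score rather than to a single contraction, the right-hand column is the relevant one. On that column, ICC 0.80 would give −0.25 and ICC 0.98 would give −0.08.

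**4. Practice gain.** With a day-2 gain of 0.5 SD that is retained at follow-up, the simulated artefact relative to the practised level is −0.35 SD: smaller, with the same sign.

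**5. Chance of a spurious fall.** In 20,000 simulated trials under step 2 (paired t test, two-sided 5%, no Tukey adjustment), one arm of 25 showed a significant fall in about 55% of trials with no true change in any patient. The figure was 38% when individual true changes averaged zero with an SD equal to the within-person SD. Tukey adjustment would lower both.

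**6. Between-arm contrast.** In the same setting the mean difference in change between two arms was about 0 (0.002 SD), with type I error 0.05. The offset is common to the arms and cancels.

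**7. Only 10 of 75 retested.** The average artefact is (10/75) × 0.564 = 0.075 SD, or about 0.075 × 0.316 = 0.02 in d at ICC 0.90. The retested 10 then have a best-of-two-days baseline and the other 65 a single-day baseline.

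**The case against.** The best defence is that the handgrip text states a general rule of two days and does not confine it to baseline. Applied at both times, it produces no bias. The single follow-up day comes from a short visit list in an article that condenses a fuller protocol. This stands in part: the authors may have intended two days at each time. The follow-up list and the Fig. 2 caption then lack the second day, so the text still needs correcting.

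Second, the data-analysis section puts test-retest in 10 subjects, and typical error is the stated purpose of Visit 4. On that reading most patients have one day at both times and the average artefact is negligible. This also stands as a possible reading. It conflicts with the Setting and functional-test sections, which state no such limit, and it leaves a scoring rule that differs between patients.

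Third, the trial compares randomised groups, and handgrip is one item within one secondary outcome. This stands fully. A reader might infer that the between-arm handgrip comparison is biased, but the documents do not support that. The offset is shared, and Visit 4 precedes randomisation, so retesting cannot depend on the assigned arm. A sub-sample of 10 could be unevenly spread only by chance.

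A reader might also infer that every reported handgrip effect size is wrong by construction, or that controls are bound to appear weaker. Both go too far. The first depends on which reading of the schedule applies. The second assumes no true change and no further practice gain at the later test.

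**Conclusion.** The point holds in conditional form. If all patients are retested at baseline and follow-up is Visit 11 alone, the handgrip time effect and within-group Cohen's d are biased downward by about 0.42 to 0.56 within-person SD. That is roughly −0.09 to −0.18 in d at assumed reliability of 0.95 to 0.90. Given unequal numbers of test days, the direction is secure, because a maximum over two days is never below either day. The size in kilograms cannot be computed from the article.

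If only the sub-sample of 10 is retested, the average bias is about −0.075 SD, with inconsistent scoring across patients as the remaining fault. Between-arm contrasts are unbiased in expectation under either reading, and MADRS is untouched.

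The severity is minor. The shift lies within the article's own small band (up to 0.49), although it could carry an arm across the 0.50 or 0.80 cut-off.

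**What to change.** Reconcile the Setting section, the follow-up visit list with the Fig. 2 caption, the handgrip paragraph and the data-analysis section on two questions: how many handgrip test days apply before and after training, and who is retested. Then score handgrip identically at both times for every patient, as the best of three contractions on one pre-named baseline day and at Visit 11. Use the other baseline day only for the typical-error estimate. Either Visit 3 or Visit 4 can be named, provided this is done in advance. The article describes no handgrip familiarisation (its familiarisation trials are for the Timed Up and Go test), so it gives no documented reason to prefer Visit 4.

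The cost is a sentence or two of text and a slightly noisier baseline value; no extra visit or test is needed. Keeping the two-day rule and adding a second follow-up test day for everyone would also remove the mismatch, at the price of an additional test day per patient.
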